### Methods in analysis to handle protocol non-adherence and any statistical methods to handle missing data {20c}

Per-protocol analyses will be conducted for the primary and major secondary outcomes using the same methods as for the interim analyses. The per-protocol analysis dataset will include all infants who received the randomized intervention (routine care or intervention).

If missing data occurs, it will be assumed to be noninformative (missing at random), and it will be imputed under a Bayesian framework by simulating from the posterior predictive distribution.

### Plans to give access to the full protocol, participant-level data, and statistical code {31c}

We will grant public access to the full protocol, participant-level dataset, and statistical code upon request within 1 year after the publication of the study. We will foster collaboration, facilitate replication, ensure transparency, and provide independent data analysis opportunities.

## Oversight and monitoring

### Composition of the coordinating center and trial steering committee {5d}

The trial will be overseen by a dedicated group of research coordinators and the trial steering committee (TSC) to ensure its quality, integrity, and adherence to regulations. The research coordinators are responsible for day-to-day operations, including screening and consenting participants, managing data collection, and ensuring regulatory compliance. The TSC will provide oversight and will meet at least twice a year and more often if needed. This committee will comprise experienced trialists, a pediatric pharmacist, a health economist, a statistician, and the medical directors of the NICU and follow-up clinic.

### Composition of the data monitoring committee, its role and reporting structure {21a}

The data monitoring committee will comprise two independent members with expertise in neonatal research: [name], MD, and [name] [name], MD. Additionally, a qualified statistician, [name], will be included to provide statistical expertise. They will review the interim analysis results when half the patients have reached 36 weeks’ PMA.

### Adverse event reporting and harms {22}

The research team perform daily monitor for any adverse event related to excessive vitamin D intake. If hypercalcemia (serum calcium >10.5 mg/dl or ionized Ca >1.55 mmol/l) is present, other laboratory parameters, such as phosphorus or magnesium, will be considered. It is common in this population to have high calcium levels with low phosphorus while in parenteral nutrition due to unadjusted calcium/phosphorus ratios. If that is the case, we will recommend modifications to the clinical team and monitor closely. If hypercalcemia occurs and other causes (e.g., low phosphorus) cannot be excluded, the NICU medical director will be contacted to determine if signs of vitamin D toxicity are found (nephrocalcinosis, trismus, feeding intolerance), stop the study drug, and notify the parents and IRB.

Due to the high mortality in the more immature infants in the study (22–25 weeks), only if unexpected or inexplicable death happens will it be communicated immediately to the IRB. If not, twice a year, a report of severe adverse events (deaths) will be shared with the IRB as part of the follow-up evaluation to allow the study to continue.

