### Criteria for discontinuing or modifying allocated interventions {11b}

Two independent blinded-to-treatment group investigators review the electronic medical records of the study infants daily during their admission to the NICU. The study drug will be discontinued if vitamin D toxicity is suspected, at the attending physician’s discretion, and for the period the infant is not receiving feeding during the intervention period.

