### Procedure for unblinding if needed {17b}

If there are concerns for vitamin D toxicity, the study drug or placebo will be stopped without unblinding the NICU staff and research team. The study statistician, NICU medical director, and the Institutional Review Board (IRB) will be notified of any infant considered to have signs suggestive of vitamin D toxicity and any infant with a serious adverse event by the National Institute of Health definition [28].

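### The hypercalcemia escalation rule in {22} omits, as worded, the infant whose other causes have been ruled out, and overlaps with the low-phosphorus pathway (minor)

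*Protocol article*

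**What the plan says.** Section {22} (Adverse event reporting and harms) handles a high calcium value in three steps.

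1. A threshold and a laboratory check: "If hypercalcemia (serum calcium >10.5 mg/dl or ionized Ca >1.55 mmol/l) is present, other laboratory parameters, such as phosphorus or magnesium, will be considered".
2. A benign pathway. The section notes that high calcium with low phosphorus is common in these infants during parenteral nutrition, and continues: "If that is the case, we will recommend modifications to the clinical team and monitor closely".
3. An escalation pathway: "If hypercalcemia occurs and other causes (e.g., low phosphorus) cannot be excluded, the NICU medical director will be contacted". The director's task and the further actions follow: "to determine if signs of vitamin D toxicity are found (nephrocalcinosis, trismus, feeding intolerance), stop the study drug, and notify the parents and IRB".

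Three other sections bear on the same infant.

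- {11b} provides surveillance, in that two blinded "investigators review the electronic medical records of the study infants daily during their admission to the NICU", and a general stopping rule: "The study drug will be discontinued if vitamin D toxicity is suspected". The attending physician may also stop the drug.
- {17b} says "If there are concerns for vitamin D toxicity, the study drug or placebo will be stopped without unblinding". It adds a notice: "The study statistician, NICU medical director, and the Institutional Review Board (IRB) will be notified of any infant considered to have signs" suggestive of toxicity, or with a serious adverse event. Parents are not on that list.
- {21b} allows the trial to stop for biochemical signs of toxicity only if they persist, have no other explanation and occur in multiple infants. Its criteria include phosphorus above 4 mg/dl.

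**The concern.** In a toxicity rule, ruling out other explanations should raise suspicion of the study drug. The condition in {22} works the other way at one end: once other causes are excluded, the infant no longer meets it. That infant is the one for whom the director's assessment is most needed.

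This is an instruction that daily reviewers apply to individual infants, some of them receiving 800 IU/day on top of parenteral or fortified-feed vitamin D. At stake is whether staff following {22} have a clear trigger for the right infant. Power, sample size, the primary outcome and the interim rule are not affected.

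**Working it through.** No arithmetic applies. The check sets the literal conditions side by side.

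**Step 1: what the other causes are.** The example in the escalation sentence is low phosphorus. The preceding sentences present low phosphorus on parenteral nutrition as the common, benign explanation. The phrase therefore cannot mean vitamin D toxicity itself; it means explanations other than the study drug.

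**Step 2: what {22} instructs for each state of the other cause, given hypercalcemia.**

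| State of other cause | Modify-and-monitor condition met? | Escalation condition met? | Result as written |
|---|---|---|---|
| Established (low phosphorus on parenteral nutrition) | Yes | Yes, literally: a cause that is present has not been excluded | Two instructions |
| Uncertain | No | Yes | Escalate |
| Excluded | No | No | No action pathway |

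Reading the sentences in order, so that the benign pathway takes precedence, removes the double instruction in the first row. It does nothing for the third row.

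**Step 3: comparison with {21b}.** The interim rule counts biochemical signs only when nothing else explains them, and its phosphorus criterion (above 4 mg/dl) points the same way. Excluding other causes strengthens the signal there; in {22} it takes the infant out of the trigger.

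**Step 4: what still protects the excluded infant.**

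- Stopping study drug: {11b} acts on suspicion and {17b} on concern. Unexplained hypercalcemia reasonably meets both.
- Surveillance: {22} opens with daily monitoring for adverse events of excess vitamin D, and {11b} adds daily record review.
- Notice to the statistician, director and IRB: {17b} provides it, but on the toxicity route only for an infant already considered to have suggestive signs. Whether hypercalcemia alone counts as such a sign is not stated.
- Director's assessment for nephrocalcinosis, trismus and feeding intolerance: these signs are named only in the {22} sentence.
- Notification of parents about suspected toxicity: stated only in the {22} sentence.

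The last two items are where the explicit trigger is missing.

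**Step 5: the same states under the proposed wording** (escalate unless another cause has been established). Established: modify and monitor. Uncertain: escalate, as now. Excluded: escalate. Each state has exactly one instruction, and the direction agrees with {21b}.

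**The case against.** The strongest reply is that the intent is plain. The section deals with the benign low-phosphorus case and then escalates the rest, and {21b} states the principle. A clinician told to escalate when the cause is uncertain would hardly decline when no other cause remains. Looking for toxicity, moreover, does not depend on this sentence, because {11b}, {17b} and the opening of {22} all require vigilance or stopping. Much of this stands, and it is why the point is minor. It does not make the wording right. Two natural repairs treat the uncertain infant differently: requiring that other causes be excluded would drop that infant from escalation, while requiring that no other cause be established keeps the infant in. Staff should not have to choose between them.

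A second reply is that a journal article leaves notification procedure to the full protocol. That would answer a complaint that detail is absent. Here the article states the rule and its condition, and the condition as stated is wrong.

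Two stronger readings are tempting and are not supported.

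- A reader might infer that the condition is simply reversed and should be flipped. Escalating the uncertain infant is sensible and should be kept, so the condition is better described as incomplete and overlapping.
- A reader might infer that the excluded infant would stay on study drug, or might count how many of the escalation actions are lost. The documents do not support the first, given {11b} and {17b}. Nor do they support a count: {22} makes contacting the director and determining signs one step, and the {17b} toxicity notice presupposes that signs are already considered present.

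**Conclusion.** The escalation sentence in {22} is wrong as written, and the point is minor. Taken literally, it gives no action pathway to the infant whose other causes have been excluded, overlaps with the modify-and-monitor pathway for low phosphorus, and conflicts with the direction of the interim rule in {21b}. It is probably a drafting slip.

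The practical gap is limited to the explicit trigger for the director's assessment of the named signs and for parent notification. This rests on two assumptions: that staff apply {22} as worded, and that unexplained hypercalcemia counts as suspicion or concern under {11b} and {17b}, so that study drug is stopped regardless. The article gives no rate of hypercalcemia, so the number of infants affected cannot be stated.

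**What to change.** Reword the condition in {22} along these lines: *If hypercalcemia occurs, then unless another cause (for example, low phosphorus on parenteral nutrition) has been established, the NICU medical director will be contacted …*, leaving the actions that follow unchanged. Add a cross-reference to the stopping rule in {11b} and the notification rule in {17b}.

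The cost is one phrase of protocol text, IRB approval before it takes effect as {25} requires, and a note to the daily reviewers. Because {25} applies changes only to infants enrolled afterwards, a clarifying note is the quicker route for infants already in the trial. No new tests are needed: serum calcium and phosphorus in the first 28 days are already among the outcomes in {12}. The downside is possibly a few more escalations.

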### Frequency and plans for auditing trial conduct {23}

The study team will audit the data regularly. The IRB, the Food and Drug Administration, and the Office of Human Research Protections will have access to the study records per request.

### Plans for communicating important protocol amendments to relevant parties (e.g., trial participants, ethical committees) {25}

The IRB will receive any protocol modifications, which will not occur until approval. The consent form will include the changes, and only the patients enrolled after the changes take place will be affected. ClinicalTrials.gov and sponsors will be notified of the changes.

### Dissemination plans {31a}

Our parent advisory board will collaborate on a clear summary for study participants, sharing personalized letters via mail and a dedicated website. Healthcare professionals will access results on ClinicalTrials.gov and the publication of the results in a reputable journal, through webinars and conferences. Public dissemination will be facilitated through social media and our study website, ensuring accessibility, and understanding for a lay audience.

## Discussion

While supplementation with up to 1000 IU/day may be used in many places, we chose 800 IU/day as the intervention arm because it is unlikely to cause toxicity even in EP infants [5]. A fixed rather than a weight-based dose is used because the smaller and more preterm the infant, the higher the risk for vitamin D deficiency, the longer it takes to reach full feedings [14, 35], and the greater the need for growth. Moreover, EP infants may also need a rapid increase in vitamin D levels after birth to optimize intracellular transport [10].

The needs for vitamin D and the metabolism in EP infants may differ from other populations [36, 37]. We will correlate the supplementation regimen, vitamin D metabolite levels analyzed by state-of-art, and clinical outcomes in EP infants. Our findings will help identify levels associated with the best clinical outcomes and avoid assuming that values considered normal in larger and older infants should be the goal values for EP infants [38, 39].

Our measure of respiratory support is ordinal. This avoids using a primary composite outcome (e.g., death or BPD), which gives equal statistical weight to outcomes of differing importance. Moreover, the ordinal outcome allows greater statistical power and a more meaningful assessment [40, 41]. Limitations of traditional frequentist analyses are increasingly recognized, and dichotomous conclusions based on arbitrary *p* value thresholds are increasingly criticized [18, 19]. Bayesian analyses avoid these problems and allow direct assessment of the probability of treatment benefit—what clinicians, patients, and family members want to know—which is not obtainable with standard frequentist analyses [20, 21]. These advantages are particularly important in studies with limited sample size [22]. The posterior probability of benefit will be assessed using conservative neutral prior estimates with a 95% CrI within the range for clinical outcomes almost always found in major randomized trials (RR = 1.0; 95% CrI = 0.33–3.0).

During our trial, we will survey different stakeholders (neonatologists, a random sample of neonatal bedside nurses, and the medical and nursing directors of our NICU) about potential barriers to adopting and implementing higher-dose vitamin D supplementation if our hypotheses are confirmed. This information will position our investigator team to have the largest and quickest impact on patient care after trial completion [42].

If our hypotheses are correct, the results may change clinical practice in conjunction with the supportive findings of prior or future trials. Even if a benefit is not shown, the study will advance the understanding of vitamin D metabolism in EP infants and help determine target 25-OH-D_3_ levels associated with the best clinical outcomes.

## Trial status

The protocol version number NCT05459298 is on ClinicalTrials.gov. The registration date was on July 14, 2022. Enrollment started on September 6, 2022, and enrollment to date is on schedule. The approximate date when recruitment will be completed is on July 1, 2025.

## Data Availability

The dataset to be collected and analyzed for this study will be available by contacting the corresponding author upon reasonable request.

## Abbreviations

25-OH-D_3_: 25-Hydroxy vitamin D3
BSID-IV: Bayley Scales of Infant and Toddler Development, fourth edition
BPD: Bronchopulmonary dysplasia
BW: Birth weight
CA: Corrected age
CrI: Credible interval
EP: Extremely preterm
GA: Gestational age
IDP: Investigational drug pharmacy
IRB: Institutional Review Board
MCMC: Markov chain Monte Carlo
NDI: Neurodevelopmental impairment
NICU: Neonatal intensive care unit
PMA: Postmenstrual age
REDCap: Research Electronic Data Capture
RR: Relative risk
SD: Standard deviation
ViDES: Vitamin D Extra Supplementation Trial
